### Secondary objectives and secondary endpoints

The secondary objectives will be to evaluate the impact of a strategy of RASi continuation or discontinuation on per-anesthesia severe hypotension episodes, on postoperative mortality, and on episodes of acute kidney injury and hyperkalemia. Secondary endpoints will therefore be:episodes of hypotension requiring vasopressors administration during anesthesia and surgery. We define hypotension as a mean arterial pressure < 60 mmHg. All types of vasopressors will be considered (i.e. ephedrine, epinephrine, norepinephrine, or neosynephrine). Bolus and continuous infusion will be considered. Lowest arterial pressure, duration of hypotension, and total doses of vasopressors will also be collected and reported;episodes of hyperkalemia requiring therapeutic intervention;Acute kidney injury (according to the KDIGO criteria based on serum creatinine changes) [23];maximum SOFA (sequential organ failure assessment) score from postoperative day 1 to day 7 in patients admitted to ICU;duration of hospital stay (patients who will be outside the hospital but in other types of healthcare facilities at day 28 will be considered to have been discharged home);hospital-free days (censored at 28 days following surgery);all-cause mortality 28 days after randomization;Intensive Care Unit length of stay (when applicable); andhospital length of stay.

### Description of parameters for assessing efficacy endpoints

The primary endpoint is a composite endpoint, which will be collected at each visit. Diagnosis of complications will be made by investigators (anesthesiologists for medical complications and surgeons for surgical complications) and/or a specialist if he or she has been consulted for a complication. Because a double-blinded trial was not feasible (i.e. due to the higher number of medications containing an ACEi or ARB), an endpoint adjudication committee will review all events. Research assistants and experts of the adjudication committee will be blinded to the group assignment. Clinicians in charge of the patients will not be blinded. The endpoint adjudication committee will review clinical data and adjudicate efficacy endpoints while blinded to the assigned study drug group. The adjudication committee will be composed of physicians (cardiologists, neurologists, nephrologists, anesthesiologists) not participating into the study as investigators who will be provided with available collected data during the conduct of the study.

### Data management

All information required according to the protocol is entered in the case report forms. Data entry will be carried out on electronic media via a web browser. The data are collected as and when they are obtained and clearly recorded in these case report forms. Each missing data item must be coded. Clinical research associates (CRA) carry out regular follow-up visits at the study sites, after completing their initial visits. Monitoring the study will verify that the research patients are safe, protected, and their rights are being met, the data being recorded is accurate, complete, and consistent with the source documents, and the study is being carried out in accordance with the current version of the protocol, with all statutory and regulatory requirements. The investigator is responsible for the accuracy, quality, and relevance of all the data entered. In addition, the data are immediately verified as they are entered with consistency checks. The investigator must validate any changes to the values in the case report form. During or after the clinical study, the data collected about the research patients and sent to the sponsor by the investigators (or collaborators) will be anonymized. The anonymity of the patients will be ensured by reference to the first three letters of the name or initials of the full name of the person undergoing research on all documents related to the research protocol. Any suspected unexpected serious adverse reaction must also be declared electronically using the Eudravigilance European adverse drug reactions database managed by the European Medicines Agency (EMA). The sponsor must notify all the investigators any information that could adversely affect the safety of the participants. Assistance Publique Hôpitaux de Paris (AP-HP) is the sponsor of this study and has delegated power to its Clinical Research and Development Department (DRCD) in order to conduct the study in accordance with Article L.1121–1 of the French Public Health Code. AP-HP reserves the right to terminate the study at any time for medical or administrative reasons. In this case, the investigator will be informed accordingly.

In the case of lost-to-follow-up, the investigator will do his or her best to contact him or her in order to know whether he is alive. Mailing address, phone number, and phone number of at least one relative will be collected at inclusion to contact the patient. If an individual leaves the research prematurely, data relating to the participant can be used unless an objection was recorded when the patient signed the consent form. If consent is withdrawn, no data about the individual may be used unless he/she states in writing that he/she does not object. In practice, the participant is excluded from the research (Fig. 3 and Additional file 2).

**Fig. 3 Fig3:**
[figure not shown]
CONSORT *flow chart* of the study

It should be noted that all amendments will be validated by the institutional review board and, once validated, the content of the amendments will be communicated to all investigators through contact emails, newsletter (on a three-month basis), and during the investigators meeting.

### Description of statistical methods

Main analysis will be by intention-to-treat comparing the composite outcome measure at 28 days in the two groups by chi-squared test (or Fisher’s exact test as appropriate). Based on an incidence of 25% of the primary endpoint in the reference group, a total of 2222 patients will allow a 80% power to detect a 20% relative decrease of complications in the experimental group (corresponding to an absolute decrease of incidence of the primary endpoint of 5%) using a Chi-square test and considering that the two interim analyses will lead to a final test at a nominal alpha value of 0.0465 according to the O’Brien and Fleming principle. More detailed statistical analysis can be found in the Additional file 2. Sample size calculation was performed using the nQuery Sample Size Software (Statistical Solutions Ltd., Cork, Ireland), statistical analysis will be performed using SAS 9.4 (SAS Institute Inc., Cary, NC, USA).

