## Methods

### Design

The protocol was designed in accordance to the guidelines [18] (Fig. 1). This is a multicenter, open-labeled randomized controlled trial (RCT) in > 30 French centers. The randomization is performed at the CRU “Lariboisière-St Louis” and stratified by center and on the chronic heart failure status (New York Heart Association [NYHA] stage ≥ 2). The randomization list has been developed by a different biostatistician from the biostatistician who will conduct the final analysis within the CRU “Lariboisière- St Louis.” The list is inserted into the web-based software and then forwarded to the sponsor’s quality insurance team for validation. The patients are randomized on the day of written consent obtainment by web (CleanWeb) software, which assigns the patient a randomization number. Randomization is performed by blocks of four or eight with allocation concealment.

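### The primary chi-square ignores the randomization strata: it is valid and powered as stated, but somewhat conservative if center and heart failure predict the outcome, and it forgoes a small gain in power

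*Protocol article*

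**What the plan says.** The protocol article's Design section describes a "multicenter, open-labeled randomized controlled trial (RCT) in > 30 French centers". Randomization is "stratified by center and on the chronic heart failure status", the latter defined as NYHA stage 2 or higher. On blocking it says: "Randomization is performed by blocks of four or eight with allocation concealment". More than 30 centers by two heart failure levels makes more than 60 strata.

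The section Description of statistical methods fixes the main analysis, by intention to treat, as "comparing the composite outcome measure at 28 days in the two groups by chi-squared test", with Fisher's exact test as the fallback. It names no stratification or adjustment. The sample size uses the same test. The control rate is given as "Based on an incidence of 25% of the primary endpoint in the reference group", the target as a "20% relative decrease of complications in the experimental group" (25% to 20%), and the size as "a total of 2222 patients will allow a 80% power". Two interim analyses "will lead to a final test at a nominal alpha value of 0.0465". The section sends the reader to Additional file 2, which was not available, for more detail.

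**The concern.** Blocked randomization within strata forces near-balance on center and heart failure, so differences in risk between strata largely drop out of the treatment comparison. A crude two-by-two chi-square still counts those differences in its variance. If the strata are prognostic, the standard error is too large for the design, the interval is too wide and the test rejects less often than its nominal level.

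Both factors could plausibly matter here. The composite includes acute pulmonary edema, cardiogenic shock and severe arrhythmia, which bear on heart failure. It also includes unplanned ICU admission, non-invasive ventilation and reoperation, which depend on local practice and case mix. At stake is precision that the design has already secured and the analysis does not use.

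**Working it through.** **Inputs from the article:** 25% v 20%, N = 2222, power 80%, final alpha 0.0465, chi-square test. **Assumed because not stated:** two-sided test and 1:1 allocation, so 1111 per arm. A one-sided test would need only 1772 in total, which does not fit.

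**Step 1, the stated size.** n per arm = [z(1−α/2)·A + z(0.80)·B]² / d², with A = √(2 × 0.225 × 0.775) = 0.5906, B = √(0.25 × 0.75 + 0.20 × 0.80) = 0.5895 and d = 0.05. This gives (1.9908 × 0.5906 + 0.8416 × 0.5895)² / 0.0025 = 1118 per arm, 2236 in total, within 0.6% of 2222. At 1111 per arm, power = Φ[(0.05 × √1111 − 1.9908 × 0.5906) / 0.5895] = Φ(0.833) = 79.75%. The stated 80% is therefore the power of the unstratified test itself.

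**Step 2, approximate formula for the strata.** Let R² be the between-stratum variance of the event probability divided by p(1−p), and s = √(1−R²). Under the null the crude z has standard deviation s, so:
- actual alpha = 2[1 − Φ(1.9908/s)];
- excess width of the crude interval = 1/s − 1;
- crude power = Φ[(d√n − 1.9908·A)/(B·s)];
- stratified power = Φ[(d√n − 1.9908·A·s)/(B·s)].

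Assumed: 15% of patients with NYHA stage 2 or higher, and center effects normal on the logit scale.

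| Center SD, heart failure OR | R² | Actual alpha | Interval too wide by | Crude power | Stratified power |
|---|---|---|---|---|---|
| 0.3, 1.5 | 2.1% | 4.4% | 1.1% | 80.0% | 80.6% |
| 0.5, 2 | 5.6% | 4.0% | 2.9% | 80.4% | 82.0% |
| 0.7, 2 | 9.2% | 3.7% | 4.9% | 80.9% | 83.5% |

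For scale, around a center with 25% risk, an SD of 0.5 puts centers one SD away at about 17% and 35%.

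The formula ignores information lost in small strata, so it slightly overstates the gain. For the same three scenarios, a simulation with 35 unequal centers and blocks of 4 and 8 (6,000 trials each) gave gains of about 0.3, 1.2 and 2.1 points.

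**Step 3, larger simulation, including weak effects.** 60,000 trials per scenario, N = 2222, 32 unequal centers by heart failure, near-balance within each stratum. Crude chi-square and Cochran-Mantel-Haenszel (CMH) were both tested at two-sided 0.0465.

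| Assumed stratum effects | Crude power | CMH power | Crude alpha | CMH alpha |
|---|---|---|---|---|
| None | 79.5% | 79.2% | 4.7% | 4.8% |
| Heart failure only (OR 2, 10% prevalence) | 80.0% | 80.1% | 4.7% | 4.8% |
| Same, plus center SD 0.3 | 80.2% | 80.6% | 4.3% | 4.5% |
| Same, with center SD 0.5 | 80.4% | 81.5% | 4.1% | 4.5% |
| Center SD 0.7, OR 2.5, 20% prevalence | 81.1% | 83.6% | 3.8% | 4.8% |

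The Monte Carlo standard error is about 0.16 points for power, √(0.8 × 0.2/60,000), and 0.09 points for alpha. An extreme case (center SD 1.0, OR 3, 20% prevalence; 10,000 trials) gave 81.4% v 85.8% and a crude alpha of 3.1%. It shows the trend continuing and is not relied on.

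**The case against.** The strongest defense is that analysis and sample size use the same test. A reader might infer from the mismatch that the trial falls short of its planned power. The article does not support that: crude power stays at about 80% in every scenario and rises slightly as the strata become more prognostic. What is given up is a possible addition. Nor can one infer inflated error, since the bias is toward conservatism and a positive result would not be in doubt. These objections stand.

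It also stands that the effect is conditional. The article gives no heart failure prevalence, center variation or odds ratio. With no stratum effect CMH is about 0.3 points worse, and with heart failure alone the two tests are practically equal.

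Additional file 2 may contain a stratified or adjusted analysis, so one cannot say that the trial plans none. That answers only part of the point, because the article itself names the chi-square as the main analysis.

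Finally, stratifying has a price. Many of the more than 60 strata will be small, a stratum with patients from only one arm contributes nothing to CMH, and this is worse at the interim looks. That price is real but small: in the final-analysis simulations CMH held its level (4.5% to 4.8%) despite the sparse strata.

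**Conclusion.** The point holds as one of efficiency and consistency between design and analysis. It is not a validity error. The unstratified chi-square is valid and gives roughly the stated 80% power. If center and heart failure status predict the composite, it is conservative: about 3.7% to 4.5% actual type I error against 4.65% nominal across the mild to strong scenarios, with an interval about 1% to 5% too wide. It then forgoes roughly 0 to 2.5 points of power at the same N. The direction is secure. The size rests on assumed center variation, heart failure odds ratio and prevalence, and center sizes, together with a two-sided test and 1:1 allocation.

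**What to change.** Make the primary analysis a Cochran-Mantel-Haenszel test, reported with a stratified risk difference and relative risk, by NYHA stage 2 or higher and center. A model adjusted for both factors and standardized to a marginal risk difference is an acceptable alternative, though center effects for more than 30 sites bring sparse-data problems of their own. Fix in advance a rule for pooling small centers that does not depend on arm or outcome. Use the same test at both interim looks and the final one, and keep the crude chi-square as supportive. If Additional file 2 already plans a stratified analysis, state there and in the main text which analysis is primary.

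The cost is wording in the protocol and SAP before unblinding. No new data or patients are needed. The downsides are the pooling rule, sparse strata (chiefly at the interim looks), and at most about 0.3 points of power if the strata turn out not to be prognostic.

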## Discussion

In this RCT, we aim to evaluate the impact of a strategy of RASi continuation or discontinuation on perioperative complications in patients undergoing major non-cardiac surgery. Chronic treatment with RASi is highly prevalent in patients undergoing major surgery but lack of evidence has led to conflicting guidelines regarding the best management of these medications. The results of the trial should impact guidelines regarding management of RASi with higher level of evidence to anesthesiologists and surgeons before major non-cardiac surgery [24].

## Trial status

The first version was published on 15 December 2018 and was last updated on 2 July 2018 (including adjustment on the definition of major surgery). Study recruitment started on 6 February 2018. The estimated study completion date is 6 April 2021. AP-HP will be mentioned in the affiliation of the authors. Each site principal investigator will be listed as an author from the second author based on the number of patients included on each site (if at least one patient is included from the site). All other investigators will be listed as collaborators.

## Abbreviations

ACE-Is: Angiotensin-converting enzyme inhibitors
AKI: Acute kidney injury
ARBs: Angiotensin receptor blockers
KDIGO: Kidney Disease Improving Global Outcomes
NYHA: New York Heart Association
RASi: Renin-angiotensin system inhibitors
